### Research procedures

For the first stage of this research, interviews will be conducted with a senior manager (eg Call-centre or Human Resources Manager) within the call-centres. These interviews will aim to assess the organisation's communication and training needs and will be via telephone or face-to-face, whichever is the most convenient for the manager. Current occupational safety and health roles will be identified and the analysis of this information will further inform the measurement tool. Secondly, a large scale epidemiology study will be conducted consisting of an online biopsychosocial questionnaire, which will be administered to investigate the work environment and vocal demands of call-agents. This will be published on a secured website and accessed at a convenient time, in agreement with the management team in the call-centres. Participants will receive information on the study including the time required for completion and assurance that all responses are anonymous. The third and final stage will involve acoustic measurement from a monitored telephone call-sample of a random sample of participants, who participated in the online survey. A sample of the natural conversation will be selected by a call-centre staff member and given to the research team in digital format for analysis.

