### Participants

The research participants will be employees from call-centres throughout the UK and Ireland. As this is a relatively new area of research, the main measurement tool, biopsychosocial questionnaire for the online survey will be developed to collect the relevant information to meet the aim and objectives of this study, thus power calculations were not calculated. The sample sizes of the participants in each stage of this study are as follows: 1. interviews with one manager from each participating call-centre (at least 10 call-centres); 2. online survey will be completed by a purposive sample of at least 500 call-agents from the participating call-centres; and 3. acoustic measurements will be conducted from at least 10% of participants from stage 2. It is anticipated that these sample sizes should be sufficient for the measurement tools to collect information on the vocal demands, communication, vocal health and training needs of call-agents in call-centres within the UK and Ireland. The findings from this study will be used to calculate a power calculation for the follow-up randomised controlled trial in call-centres.

The Human Resource department of each call-centre in the UK and Ireland will be contacted via e-mail inviting participation in this research study. Interested call-centres will contact the research team and receive full details of this study, and a manager from the participating organisations will provide written informed consent. The management team within the participating call-centres will inform their call-agents of this study and invite them to complete the online survey. The first question on the questionnaire for the online survey will ask the call-agents to indicate consent.

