Acoustic analysis will be conducted on a random sample of the voice of call-agents from call-samples using the Multi Dimensional Voice Program (MDVP), which is a software programme that provides a robust multi-dimensional analysis of voice with graphic and numerical presentation of analysis [17]. MDVP is the gold standard measurement tool for quantitative analysis of voice. From the telephone call-samples, three sections each consisting of three seconds of the call-agent's continuous voice uninterrupted by the customer will be selected during 10 seconds at the first, middle and the end of the call. Three seconds of recording is within the recommended range for acoustic analysis by the manufacturer of the voice analysis software [17]. Therefore three sections (start, middle and end) of each call-sample will be used for acoustic analysis. The voices of the call-agents in these sample-calls will be analysed for the following 14 acoustic parameters: Mean Fundamental Frequency (MFo); Highest Fundamental Frequency (Fhi); Lowest Fundamental Frequency (Flo); Standard Deviation of Fo (STD); Amplitude Tremor Frequency (Fatr); Absolute Jitter (Jita); Jitter Percent (Jitt); Shimmer in dB (ShdB); Shimmer Percent (Shim); Peak-to-Peak Amplitude Variation (vAm); Noise to Harmonic Ratio (NHR); Degree of Voice Breaks (DVB); Degree of Sub-harmonics (DSH); and Degree of Voiceless (DUV). In addition, the acoustic results will be integrated into the voice measurement model using SEM.

All numerical data will be analysed using SPSS version 15. Descriptive statistics will include means, standard deviations and ranges for each variable from the online survey and acoustic analysis. Inferential statistics such as Pearson Correlations will be used to compare the objective and subjective measures. If the assumptions for the above parametric tests are violated then the appropriate non-parametric tests such as the Mann-Whitney will be used.

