### Ethical issues

This study has obtained ethical approval from the School of Communication Risk and Ethics Filter Committee, University of Ulster. The questionnaires and the telephone call recordings will be anonymous. These will only be identified by code and not by individual call-agent's or customers' name. There are no known risks in this study.

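### Agents are assured that their data are anonymous, but stage 3 links each sampled agent's calls to that agent's questionnaire, which needs coded, re-identifiable data

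*Protocol article*

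**What the plan says.** Four parts of the protocol article bear on this.

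- **Research procedures, survey stage.** Participants are given "assurance that all responses are anonymous", with no qualification.
- **Research procedures, acoustic stage.** The third stage is "acoustic measurement from a monitored telephone call-sample of a random sample of participants, who participated in the online survey". The extract of conversation "will be selected by a call-centre staff member and given to the research team".
- **Data analysis.** "Inferential statistics such as Pearson Correlations will be used to compare the objective and subjective measures". In addition, "the acoustic results will be integrated into the voice measurement model using SEM".
- **Ethical issues.** Questionnaires and call recordings are both described as anonymous. The next sentence adds "These will only be identified by code", as opposed to the name of the agent or customer. The section ends by stating that the study carries no known risks.

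On consent, the Participants section has a manager consent for the organisation. For the agents it says: "The first question on the questionnaire for the online survey will ask the call-agents to indicate consent".

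**The concern.** Anonymous, as an agent will read it, means that nobody can trace an answer back to the person who gave it. The design needs someone to do exactly that for every agent sampled in stage 3, and the route to the recordings runs through the agent's employer.

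The employer is the party from whom an agent is most likely to want protection. Management issues the invitation, its staff pick the call, and the questionnaire asks about voice symptoms and feelings of incompetence at work. Agents would decide whether to take part, and how candidly to answer, on an assurance that does not describe what will happen to their data. This matters statistically as well as ethically. Self-reported symptoms are the main measurement of the study, and participation and candour both depend on what agents believe about confidentiality. Agreement obtained under an inaccurate assurance is also hard to repair once the data are in.

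**Working it through.** The article has no figure to reproduce here; it states that no power calculation was made. The check is a comparison of its statements, with one line of arithmetic.

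**Step 1: what stage 3 needs**

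1. *Drawing the sample.* The frame is the survey responders, so the research team needs a list of responders.
2. *Obtaining the call.* A call-centre staff member selects the recording. Each sampled responder must therefore be translated into an agent whose calls that person can find.
3. *Pairing the data.* A Pearson correlation between an acoustic parameter and a questionnaire score needs both values from the same agent. Entering acoustic results in the same structural equation model as the questionnaire variables, at the level of the agent, needs the same.

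All three fail if no one can tie a response to a person.

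**Step 2: the two readings of anonymous**

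| Reading | Random draw from responders | Matched pairs | Assurance true? |
|---|---|---|---|
| Strict: no link exists | not possible | 0 | yes |
| Coded: a key resolves the code to an agent | possible | at least 50 | no |

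**Step 3: the number of pairs**

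Inputs from the Participants section: at least 500 agents in the survey, and at least 10% of them in stage 3.

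Minimum linked agents = 0.10 × 500 = 50.

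**Step 4: which reading the article uses**

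The Ethical issues section names a code, so the second row of the table describes the study. Linkage is feasible, but the description given to agents is wrong. That section contains both terms side by side: it calls the data anonymous and then explains how they are identified.

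**The case against.** The best reply is that the article defines its own term. Read as a whole, it uses anonymous to mean un-named and coded. A shared code allows random selection and pairing, and if the key is kept away from the employer, nobody there sees an agent's answers. This stands as far as feasibility goes. A reader might infer that the linked analyses cannot be done at all, and the article does not support that. It does not rescue the assurance, because the text in Research procedures carries no such definition, and an agent told that responses are anonymous has no reason to read it as coded.

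Some other inferences go further than the article allows.

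- *That the hypothesis on acoustic voice production becomes untestable.* Even under strict anonymity, a cruder comparison between centres could be made, because the manager interviews describe each organisation. Only the agent-level analyses depend on the link.
- *That the employer will see symptom answers.* The Data protection section limits access to the research team. Staff asked to supply a call may learn that an agent was sampled, and even this depends on how the request is made, which the article does not describe.
- *That consent to call release and custody of the key are absent.* The article does not limit the agent's consent to the survey, and it says that information on the study will be given. Such details are often left to the full protocol, so silence on them is not an error.
- *That duplicate or outside entries cannot be prevented.* The survey sits on a secured website, and nothing suggests open access.
- *That the under-reporting can be sized.* The article gives no rate at which agents would hide symptoms, so no figure for bias can be derived.

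**Conclusion.** The point holds in a limited form. The assurance of anonymity in Research procedures, repeated in Ethical issues, is untrue as worded, because the sampling frame and the planned analyses require coded data that can be traced to an agent. This affects every agent in stage 3 (at least 50 under the stated minima) and the assurance given to all of the 500 or more survey participants. Honoured to the letter, the assurance would leave the agent-level comparison of acoustic with self-reported measures without a single matched pair.

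The conclusion rests on two readings of the text: that the correlations are made within agents, which is the ordinary meaning of correlating objective with subjective measures, and that stage 3 participants really are drawn from the survey responders, as stated. It assumes nothing about the unseen full protocol. A fuller document could explain who holds the key, but it could not make an unqualified promise of anonymity true alongside a person-level link. The correction should be made before the survey opens.

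**What to change.** 1. In Research procedures and in Ethical issues, replace anonymous with confidential and coded.
2. Use a study code whose key is held only by the research team, and say so. The code should be attached to a recording by the team and not by call-centre staff, so that staff never hold the link between code and agent.
3. Tell agents, before the first substantive question, that survey and call data will be linked, and that staff who supply calls may learn who was sampled but not what was answered.
4. Ask for agreement to release of recorded calls as a separate item, or confirm that the full protocol already does. Draw the random stage 3 sample from responders who agree.
5. Compare the survey scores of those who agree with those who do not. The sample is then random only among the willing, and this comparison shows how far it may differ from all responders.
6. Amend the statement that there are no known risks so that it names possible disclosure of participation to the employer.

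The cost is a change to the participant information and the ethics text, a code on the survey site and one added question. Some agents may decline stage 3. To reach the planned minimum from 500 responders, 50 must agree (50 / 500 = 10%), so there is room for refusals. The greater cost of refusals is selection, which item 5 makes visible.

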### Data analysis

The data from the interviews will be transcribed and analysed thematically to determine context and process characteristics of each organisation. Qualitative content analysis will identify underlying themes and issues, which will be used to further refine and inform the questionnaire design.

Questionnaire analysis will account for the complex interaction of multi-factorial variables and the wide range of theoretical perspectives requiring evaluation with an appropriate range of methodological tools and approaches. Given the complexity of the study and the array of variables impacting on vocal strain, there is a need to employ sophisticated forms of analysis, with the capacity to explore potential directional effects across a wide range of variables. While multiple regression analysis is frequently used to analyse social science data, the main problem is handling measurement error, indirect or mediating effects. Since most multivariate procedures cannot deal with multiple variables, particularly multiple dependent or criterion variables, hypothesis testing is difficult.

Therefore, the study will adopt a multivariate analysis approach using Structural Equation Modelling (SEM), to develop voice measurement models in determining the construct validity of potential factors contributing to Occupational Dysphonia [16]. The research design and associated analysis will therefore attempt to overcome the traditional complications of multiple indicators, indirect effects and measurement error by using structural equation modelling with latent variables and LISREL (Linear Structural Relations) estimation. SEM is a statistical methodology that takes a confirmatory (ie hypotheses-testing) approach to the multivariate analysis of a structural theory bearing on some phenomenon, representing causal processes, which generate assumptions on multiple variables [15]. The hypotheses are: 1. Call-agents' physiological voice production is improved with good vocal-working environment; 2. Call-agents' acoustic voice production is improved with good vocal-working environment; 3. Call-agents' psychosocial health is improved with good vocal-working environment. The relationships and effects of these aetiological indicators on the 'risk' of occupational dysphonia will be explored in order to determine the relative significance of physiological, behavioural environmental and psychological indicators at varying levels of severity.

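### Agents are drawn at random for acoustic analysis, but call-centre staff select the conversation that represents each agent under no stated neutral rule, so the acoustic results could be biased

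*Protocol article*

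**What the plan says.** The sampling for the acoustic stage has three levels, all described in the protocol article.

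- **Agents.** Research procedures plans "acoustic measurement from a monitored telephone call-sample of a random sample of participants, who participated in the online survey". The randomness here attaches to participants. Participants sets the number: "acoustic measurements will be conducted from at least 10% of participants from stage 2". Stage 2 itself is "online survey will be completed by a purposive sample of at least 500 call-agents from the participating call-centres".
- **The recording for each agent.** Research procedures continues: "A sample of the natural conversation will be selected by a call-centre staff member", after which it is handed over digitally for analysis. It gives no criterion, draw or fixed rule for the choice.
- **Segments inside the recording.** Data analysis gives a specific rule: "three sections each consisting of three seconds of the call-agent's continuous voice uninterrupted by the customer will be selected", taken from a 10-second window at the start, middle and end of the call.

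Data analysis introduces the whole exercise as follows: "Acoustic analysis will be conducted on a random sample of the voice of call-agents from call-samples". The results are to be used for hypothesis 2 ("Call-agents' acoustic voice production is improved with good vocal-working environment"), within the structural equation model, and in Pearson correlations between objective and subjective measures.

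**The concern.** A random draw of agents does not make the recordings random if someone then chooses which recording stands for each agent. Here the choice falls to the employer's own staff, who have a natural interest in how their agents sound. The Background says that prolonged voice use and background voice levels load the voice or alter phonation. A preference for quiet, fluent or early-shift calls would therefore tend to remove the very loading under study.

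Two kinds of error are possible.

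- If all centres select in a similar way, the acoustic means are shifted as a description of agents' working voices.
- If selection habits differ between centres in step with the working environment, the shift becomes part of the hypothesis 2 association. It could create that association or hide it. The correlations with self-report could be distorted in the same way.

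The article relies on SEM to deal with measurement error, but a systematic difference between centres is not random measurement error. Without a record of the calls that could have been supplied, it can be neither measured nor adjusted for afterwards.

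**Working it through.** The article states no power, effect size, SD or significance level for the acoustic stage, so there is no figure of its own to reproduce. The check has three steps.

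**1. Implied sample.** The minimum is 10% × 500 = 50 agents. With at least 10 centres (Participants), that is 50 / 10 = 5 agents per centre if they are spread evenly. The standard error of an acoustic mean, in total-SD units and treating agents as independent, is 1/√50 = 0.14. Clustering within centres would widen it.

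**2. Illustrative shift in the mean.** Suppose staff pass on the best of k calls and rank them perfectly on the parameter analysed. Let ICC be the share of total variance that lies between agents. The within-agent SD is then √(1 − ICC) of the total SD, and

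shift = √(1 − ICC) × E[maximum of k standard normals].

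Both k and ICC are assumptions, as the article gives neither. The expected maxima are 0.564 (k = 2), 0.846 (k = 3) and 1.163 (k = 5). The factors √(1 − ICC) are 0.316, 0.548 and 0.707.

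| k | ICC 0.9 | ICC 0.7 | ICC 0.5 |
|---|---|---|---|
| 2 | 0.18 | 0.31 | 0.40 |
| 3 | 0.27 | 0.46 | 0.60 |
| 5 | 0.37 | 0.64 | 0.82 |

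For k = 3, for example, 0.316 × 0.846 = 0.27 and 0.707 × 0.846 = 0.60. Against the standard error of 0.14, the table runs from about 1.3 to 5.8 standard errors. More agents would shrink the standard error but not the shift.

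These values are ceilings. If perceived quality correlates only r with the parameter analysed, the shift is multiplied by r. With r = 0.5 and k = 3 it is 0.13 to 0.30 SD.

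**3. Consequence for an association.** A shift common to all centres moves the means but does not by itself create an association with environment. Bias in hypothesis 2 needs selection that varies with environment. Take an assumed extreme: best-of-3 selection in every centre with a good environment, none elsewhere, and 25 agents on each side. The spurious difference is then the full 0.27 to 0.60 SD. The standard error of the difference is √(2/25) = 0.28 SD, again ignoring clustering, so the bias is about 1 to 2 standard errors. Partial alignment or imperfect ranking would make it smaller.

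With calls drawn neutrally, the expected shift from call selection is 0 and the minimum of 50 agents is unchanged.

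**The case against.** The strongest reply is that this is a condensed article. It says who selects, and instructions to staff may sit in a fuller document. That stands in part: silence on the criterion does not show that none exists. But the article itself assigns the choice to the employer's staff, specifies the level below (segments within the call) in detail, and nowhere limits the choice at this level. The assignment is a stated design choice.

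A reader might infer more than the text supports, and four such readings should be set aside.

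- *Staff will hand-pick good calls.* The text says only that they select. A favourable direction, and variation between centres, are plausible but undocumented. For fundamental frequency measures, best has no clear direction.
- *The bias is as large as any plausible environment effect.* The article gives no effect size to compare with. The expected maximum of 0.85 for k = 3 is in within-agent SD and assumes perfect ranking, whereas staff judge by ear and there are 14 acoustic parameters.
- *The two uses of the word random contradict each other.* Under Research procedures the word is correct, because it refers to participants. The phrase in Data analysis is loose and can be read the same way, although taken at face value it extends randomness to the voice sample.
- *Hypothesis 2 rests wholly on these recordings.* The Vocology Screening Profile in the survey also has items relating to acoustic symptoms, so the SEM may have other indicators. The correlations of objective with subjective measures do depend on the recordings.

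It is also true that the questionnaire, with at least 500 agents, is the main tool and is untouched by this point.

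**Conclusion.** The point holds as a design weakness in the acoustic stage. The agent sample is random, but the choice of recording is discretionary and lies with an interested party. The acoustic means could be biased. So could the hypothesis 2 association, to the extent that it uses the recordings, and the objective-subjective correlations.

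The size is unknown. The illustrative 0.27 to 0.60 total SD rests on perfect selection of the best of 3 calls and an assumed ICC of 0.9 to 0.5, and it falls in proportion if ranking is imperfect. The documents do not show that bias will occur or which way it would run. Nor do they support a redesign comparing early-shift with late-shift calls, since no stated hypothesis concerns change within a shift. The reason to act is that the discretion can be removed cheaply beforehand and cannot be corrected for afterwards.

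**What to change.** In Research procedures, replace selection by staff with selection by the research team:

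- For each sampled study code, the team specifies the call by a random draw or a pre-fixed rule. Examples are the first monitored call after a randomly generated date and time, or a random pick from the list of the agent's available monitored calls. Staff only export it.
- If the call lacks the uninterrupted three-second segments that Data analysis requires, the next call in the pre-specified order is taken. A ban on any replacement would conflict with that requirement and shrink a sample whose floor is 50.
- Every call not supplied or replaced is logged with the reason.
- Time into shift is recorded where available and used as a covariate.
- If a centre cannot support a draw, Data analysis should stop describing the voice sample as random and state the limitation.

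The cost is a draw list to prepare and some drawn calls that prove poor or unusable. The article does not say that every call is archived with a time stamp, which is why the draw is confined to available monitored calls. Matching recordings to questionnaires already implies a link through the study code. The draw should use that same code, so that it stays consistent with the anonymity promised under Ethical issues.
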